### Data collection and management

All outcomes will be assessed using standardised procedures by trained personnel. Data will be collected at baseline and at 30, 60, 90 and 180 days poststroke. Participants who discontinue the intervention will be encouraged to complete all assessments. When in-person visits are not feasible, alternative follow-up (eg, home or phone visits) may be arranged. The patient timeline is shown in figure 1.

**Figure 1 F1:**
[figure not shown]
Flow chart of the MASTER trial. V1 screening includes prescreening of patients for inclusion criteria and inclusion for additional screening of exclusion criteria. Randomisation occurs within 7 days of stroke onset. V2 includes randomisation and initial assessments (imaging and clinical), carried out within 24 hours of beginning of intervention medication. V3 and V4 include one clinical assessment. V5 is the primary outcome time point, including both imaging and clinical assessments. V6 represents the 180 days follow-up. Telephone check-ins occur between each in-person visit. MASTER, Maraviroc for Stroke Recovery; mRS, modified Rankin Scale; NIHSS, National Institutes of Health Stroke Scale; FLAIR, Fluid-Attenuated Inversion Recovery; DWI, Diffusion-Weighted Imaging; MRSI, Magnetic Resonance Spectroscopic Imaging.

### Primary outcome

#### Upper Extremity Fugl-Meyer Assessment score at 90 days poststroke

The Upper Extremity Fugl-Meyer Assessment (FMA-UE) will be conducted at all time points by trained occupational therapists or board-certified neurologists. This 0–66 point scale is widely used in stroke research for its reliability and sensitivity to change.^9^ The FMA-UE is a validated, reliable tool for assessing upper limb motor function in stroke patients.^9^ The minimal clinically important difference (MCID) is 12.4 points for patients with subacute, moderately severe stroke.^10^ All raters will undergo training before study initiation.

### Secondary outcomes

Motor learning score (ability of a subject to learn a finger tapping sequence task with the paretic hand) at 90 days poststroke.

The motor sequence learning task assesses procedural motor learning capacity, relevant to rehabilitation outcomes and has been validated in previous studies within our own group.^11^ It will be administered at baseline and at 90 days. It consists of a finger tapping task using a commercial five-button response box. Data will be collected digitally and stored securely for analysis.

### Other outcomes

Hand dexterity (9 Hole Peg Test), grip and pinch strength (Hand/finger dynamometer), both sensitive and reliable measures of upper limb recovery,^12^ and clinical measures including National Institutes of Health Stroke Scale, modified Rankin Scale and Barthel Index. They are performed by trained, certified staff using validated tools at each visit.

Changes in functional connectivity between peri-infarct regions and motor network node, specifically focusing on the changes in structural connectivity (eg, fractional anisotropy) between peri-infarct regions and motor network nodes, changes in microstructural integrity within the peri-infarct area (eg, neurite density), and changes in neuronal viability in the peri-infarct area between randomisation and the 90-day follow-up (eg, concentrations of *N*-acetylaspartate, Creatinine, Glutamate-Glutamine complex).^13^ They will be assessed via MRI (resting-state functional MRI, multi-shell Diffusion-Weighted Imaging, 3-dimensional MR spectroscopy), using a standardised protocol on a 3T scanner. MRI data will be processed by blinded staff.

Laboratory tests include baseline blood analyses, genotyping for the CCR5-Δ32 mutation and biobanking for further biomarker studies (baseline, 90 days).

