**Methods and analysis:**

MAraviroc for STrokE Recovery is a phase II, single-centre, randomised, double-blind, placebo-controlled trial. The aim is to assess the efficacy and safety of the CCR5 antagonist Maraviroc for improving motor recovery of the upper limb after ischaemic stroke. 80 ischaemic stroke patients with moderate but incomplete upper extremity motor impairment will be enrolled within 7 days of onset. Participants will be randomised (1:1) to receive either oral maraviroc (300 mg two times per day) or placebo for 90 days in addition to standard rehabilitation therapy. The primary outcome is upper limb motor function assessed using the Fugl-Meyer Assessment for the Upper Extremity at day 90. Secondary outcomes include motor learning skills and plasticity in the peri-infarct region assessed using MRI connectivity and spectroscopy at 90 days.

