### Statistical methods for primary and secondary outcomes

Two analysis sets will be used: an intention-to-treat population (all randomised participants who received ≥1 dose, analysed per allocation) and a per-protocol population (excluding those with major protocol deviations, eg, <80% medication adherence). Missing data will not be imputed.

The primary outcome (FMA-UE) will be compared between groups using a t-test or non-parametric equivalent. An adjusted analysis using multivariate linear regression will account for stratification variables (infarct side, finger extension ability) as well as other variables like CCR5-Δ32 loss-of-function mutation carrier status to account for confounding effects on motor recovery and treatment response. Secondary outcomes will be analysed via regression models adjusted for the same covariates. Linear mixed models will include time point and group as fixed effects and participant ID as a random effect to account for repeated measures. To assess whether maraviroc promotes recovery via peri-infarct plasticity, causal mediation analysis will estimate direct and indirect effects (via changes in connectivity/metabolism from baseline to 90 days). The analysis includes three regression steps, with the indirect effect tested via the Sobel method. Weekly rehabilitation hours (during the first 90 days) will be included as a covariate. A similar approach will be applied to motor learning outcomes. Safety analyses will summarise the number and proportion of participants with ≥1 SAE, AE of special interest, or death by day 90 in each group.

Analyses will be conducted in R, MATLAB or Python using appropriate packages. Imaging data will be processed with FSL, FreeSurfer, SPM and DSI Studio, depending on modality.

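### The MRI outcomes and the mediator are changes from randomisation to day 90, but no named covariate is the patient's own baseline scan; adding it would gain precision at almost no cost.

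*Protocol article*

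**What the plan says.** Under Other outcomes, the Protocol article words every MRI measure as a change. The list opens with "Changes in functional connectivity between peri-infarct regions and motor network node", goes on to structural connectivity and microstructure, and ends with "changes in neuronal viability in the peri-infarct area between randomisation and the 90-day follow-up". The mediation analysis, under Statistical methods for primary and secondary outcomes, also uses baseline-to-day-90 changes in connectivity and metabolism as the mediator.

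The caption of Figure 1 dates the first scan: "V2 includes randomisation and initial assessments (imaging and clinical), carried out within 24 hours of beginning of intervention medication", and "Randomisation occurs within 7 days of stroke onset".

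The covariates are in the statistical methods section. The adjusted primary model uses infarct side and finger extension, "as well as other variables like CCR5-Δ32 loss-of-function mutation carrier status to account for confounding effects on motor recovery and treatment response". Then: "Secondary outcomes will be analysed via regression models adjusted for the same covariates". A further sentence says: "Linear mixed models will include time point and group as fixed effects and participant ID as a random effect". Weekly rehabilitation hours are added in the mediation part. The baseline value of an MRI measure is named nowhere.

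The Abstract (Methods and analysis) counts MRI among the secondary outcomes and describes it as "plasticity in the peri-infarct region assessed using MRI connectivity and spectroscopy at 90 days".

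**The concern.** A change score uses the baseline scan with a fixed coefficient of 1. That is the best use of it only if the first-scan value predicts the day-90 value one for one. Otherwise part of the noise in the first scan is carried into the comparison. Entering the baseline value as a covariate lets the data set the coefficient, and in large samples this is never less precise.

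At stake is the precision of the trial's mechanistic question. The sample size was set for the FMA-UE alone, so the MRI comparisons have no power calculation of their own. There would be at most 80 patients, or 64 if the planned 20% are lost.

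There is also a discrepancy in wording. The abstract and the outcomes section give the MRI measures different ranks (secondary, other) and, read literally, different quantities (value at 90 days, change).

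**Working it through.** **The plan's own figure.** Sample size estimate gives a difference of 12.4, SD 17.5, 5% type I error (taken as two-sided), 80% power and 20% loss.

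- n per arm = 2 × (1.960 + 0.842)² × 17.5² / 12.4² = 31.3, rounded up to 32, so 64 in total.
- 64 / 0.8 = 80, as stated.

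This figure rests on the FMA-UE and is not affected by the present point. It supplies the 32 per arm used below.

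**Assumed inputs.** The article gives no SD, scan-to-scan correlation or effect size for any MRI measure. Let r be the correlation between the two scans and k = SD(baseline)/SD(day 90). Variances are relative to an analysis of the day-90 value alone (= 1):

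- change without the baseline covariate: 1 + k² − 2rk
- baseline-adjusted: 1 − r²
- difference between the two: (k − r)², which is never negative

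With k = 1 these become 2(1 − r) and 1 − r², and their ratio is 2/(1 + r).

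| r (k = 1) | change | adjusted | ratio | extra CI width (√ratio − 1) |
|---|---|---|---|---|
| 0.3 | 1.40 | 0.91 | 1.54 | 24% |
| 0.5 | 1.00 | 0.75 | 1.33 | 15% |
| 0.7 | 0.60 | 0.51 | 1.18 | 8% |
| 0.9 | 0.20 | 0.19 | 1.05 | 3% |

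**When change is noisier than the day-90 value alone.** This requires 1 + k² − 2rk > 1, that is r < k/2: below 0.375, 0.50 and 0.625 for k = 0.75, 1 and 1.25.

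**Sensitivity to unequal SDs.** At r = 0.3, 0.5, 0.7 and 0.9 the ratio is 1.22, 1.08, 1.01 and 1.12 for k = 0.75, and 1.99, 1.75, 1.59 and 1.65 for k = 1.25.

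**Power, for illustration only.** Take 32 per arm, k = 1 and an effect of 12.4/17.5 = 0.709 SD. That effect is borrowed from the FMA-UE and is not an MRI figure. With s the square root of the relative variance, power ≈ Φ(0.709 / (s × √(2/32)) − 1.96). For change and adjusted respectively:

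- r = 0.3: 66.8% and 84.4%
- r = 0.5: 80.9% and 90.5%
- r = 0.7: 95.5% and 97.8%

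The day-90 value alone gives 80.9% throughout.

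**Does writing the outcome as change matter?** No, once the baseline scan is in the model. Regressing (day 90 − baseline) on arm and baseline only shifts the baseline coefficient by 1; the arm coefficient is the same as for the day-90 value. In a simulation of 4,000 trials with 32 per arm, the two arm estimates never differed by more than 1e-14. At r = 0.3 the standard error was 0.2403 for both, against 0.2946 for change without the covariate.

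**The case against.** The strongest reply is that the article never commits to the less precise analysis. It defines the outcomes as changes but does not say that they will be compared without adjustment for the first scan. The covariate list is open. The sentence on regression models covers secondary outcomes, whereas the body of the article places MRI under other outcomes. The mixed-model sentence does not say which outcomes it serves. Apart from the mediation step, no model is expressly assigned to MRI. A final statistical analysis plan is to be validated before unblinding, and covariates for a non-primary imaging outcome are commonly settled there. All of this stands, and it limits the point to an improvement of the text.

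It does not remove the point. A baseline MRI value is specific to each measure, so it does not follow from a list of shared covariates that illustrates its open part with genotype. The mediation step, where the change is used in a stated analysis, adds rehabilitation hours but not the baseline scan.

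A reader might infer three stronger things that the documents do not support:

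- **That defining the outcome as a change loses precision.** It does not; the loss comes only from leaving out the baseline covariate.
- **That the outcome must be redefined as the day-90 value.** This is unnecessary, and it would put the outcome at odds with the change-based mediator.
- **That the change comparison is biased.** Under randomisation it is unbiased. It can favour one arm only conditionally on a chance imbalance at baseline.

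On the abstract, the words on 90 days may merely name the time of assessment. The difference in rank is plainer.

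**Conclusion.** The point holds as a low-cost improvement. If the MRI changes are analysed with only the covariates the article names, the variance with equal SDs exceeds that of a baseline-adjusted analysis by 54%, 33%, 18% or 5% at assumed correlations of 0.3, 0.5, 0.7 or 0.9.

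The size depends entirely on r and k, which the documents do not give. A first scan within about a week of onset gives reason not to presume a near one-for-one relation with day 90, but nothing in the article shows that r is low. At high correlation with similar SDs the loss is small. The statement that change is noisier than ignoring the first scan holds only if r < k/2.

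The outcomes are not primary and neither the sample size nor the primary analysis is touched. The differing rank and wording between the abstract and Other outcomes can be seen on the page and need reconciling whatever r is.

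**What to change.** - In Statistical methods for primary and secondary outcomes, state that each between-arm MRI comparison, and the mediator model, includes the patient's own baseline value of that MRI measure and the stratification factors (infarct side, finger extension) as covariates.
- Leave the outcomes and the mediator written as changes if preferred; with the covariate in place the treatment estimate is identical to that for the day-90 value.
- Give the MRI measures one rank and one definition in both the Abstract and Other outcomes.

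The cost is wording and one degree of freedom per model. Both scans are already in the visit schedule, so no new data are needed, and the change can be made before unblinding.

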### Safety outcomes

CTCAE v5.0-defined AEs through 180 days, including major adverse cardiovascular events (ie, acute myocardial infarction, acute coronary syndrome, stroke, heart failure, cardiovascular and all-cause mortality, revascularisation), liver-related AEs and infectious complications. SAEs will be tracked continuously through 180 days post randomisation.

Blood samples will be collected at each visit for safety monitoring. Participants of childbearing potential will undergo a urine pregnancy test at each visit. Samples will be processed and stored under standardised conditions.

### Statistical methods

#### Sample size estimate

We estimated a sample size of 80 participants, based on a MCID for FMA-UE of 12.4 points in the early subacute phase of stroke recovery,^10^ a pooled SD of 17.5, based on the FLAME trial,^14^ a 5% type I error and 80% power and accounting for a 20% dropout or exclusion rate. We used the results of the FLAME randomised clinical trial (RCT), which investigated the effect of fluoxetine on stroke recovery. We based our estimation on this study because it is a large pharmacological RCT focusing on a similar population including patients with moderately severe motor deficits early after ischaemic stroke. No studies investing maraviroc after stroke currently exist.

### Statistical methods for primary and secondary outcomes

Two analysis sets will be used: an intention-to-treat population (all randomised participants who received ≥1 dose, analysed per allocation) and a per-protocol population (excluding those with major protocol deviations, eg, <80% medication adherence). Missing data will not be imputed.

The primary outcome (FMA-UE) will be compared between groups using a t-test or non-parametric equivalent. An adjusted analysis using multivariate linear regression will account for stratification variables (infarct side, finger extension ability) as well as other variables like CCR5-Δ32 loss-of-function mutation carrier status to account for confounding effects on motor recovery and treatment response. Secondary outcomes will be analysed via regression models adjusted for the same covariates. Linear mixed models will include time point and group as fixed effects and participant ID as a random effect to account for repeated measures. To assess whether maraviroc promotes recovery via peri-infarct plasticity, causal mediation analysis will estimate direct and indirect effects (via changes in connectivity/metabolism from baseline to 90 days). The analysis includes three regression steps, with the indirect effect tested via the Sobel method. Weekly rehabilitation hours (during the first 90 days) will be included as a covariate. A similar approach will be applied to motor learning outcomes. Safety analyses will summarise the number and proportion of participants with ≥1 SAE, AE of special interest, or death by day 90 in each group.

Analyses will be conducted in R, MATLAB or Python using appropriate packages. Imaging data will be processed with FSL, FreeSurfer, SPM and DSI Studio, depending on modality.

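### The day-90 t-test without imputation uses only participants with an observed day-90 FMA-UE, and the mixed model the plan names is not set up to give the day-90 effect

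*Protocol article*

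**What the plan says.** The abstract of the protocol article fixes the endpoint: "The primary outcome is upper limb motor function assessed using the Fugl-Meyer Assessment for the Upper Extremity at day 90". The section on statistical methods for primary and secondary outcomes compares this score between arms by a t-test or a non-parametric equivalent, with an adjusted linear regression alongside. The analysis set is "an intention-to-treat population (all randomised participants who received ≥1 dose, analysed per allocation". On incomplete data the section has one rule, with no exception for the primary outcome: "Missing data will not be imputed".

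The sample size section reaches 80 participants "accounting for a 20% dropout or exclusion rate".

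Three further statements bear on the point:

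- Data collection and management sets visits at baseline and days 30, 60, 90 and 180, and the primary outcome section has FMA-UE done at every time point.
- Data collection and management also asks participants who stop treatment to complete their assessments, and adds: "When in-person visits are not feasible, alternative follow-up (eg, home or phone visits) may be arranged".
- The statistical methods section names linear mixed models with time point and group as fixed effects and participant as a random effect. The sentence follows the one on secondary outcomes and does not say which outcome it serves.

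**The concern.** A two-sample test on day-90 scores, with nothing imputed, has no place for a participant without a day-90 score. The adjusted regression has the same limit. The plan expects some loss and answers it by enrolling more people. That protects power and does nothing about bias.

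The observed-case comparison is safe when loss is unrelated to the outcome. It is not safe when loss depends on how well people have recovered and does so differently in the two arms. Differential loss is possible here: the discontinuation criteria list liver toxicity, hypersensitivity and cardiovascular findings, and the safety outcomes include further stroke and death. The trial will hold day-30 and day-60 scores on many of the people lost, and the primary test uses neither.

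At stake is the headline estimate of a trial of 80, where a shift of a few points matters against a target of 12.4.

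**Working it through.** **1. The plan's own figure.** Inputs from the sample size section: "based on a MCID for FMA-UE of 12.4 points in the early subacute phase of stroke recovery", "a pooled SD of 17.5, based on the FLAME trial", and "a 5% type I error and 80% power and accounting for a 20% dropout or exclusion rate". Sidedness is not stated; two-sided is assumed because it reproduces the total.

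- n per arm = 2 × (1.960 + 0.842)² × 17.5² / 12.4² = 31.3, rounded up to 32, so 64 in total.
- Inflation: 64 / (1 − 0.20) = 80. The stated total reproduces exactly. A one-sided calculation gives 25 per arm and 63 after inflation, which does not match.

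The design therefore tolerates a primary comparison of 64 people.

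- 32 per arm: standard error 17.5 × √(2/32) = 4.375; 12.4 / 4.375 = 2.834; power Φ(2.834 − 1.960) = 80.9% (79.7% by the exact t-test).
- 40 per arm: standard error 3.913; power 88.7% (87.9% exact).

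If loss is unrelated to outcome, this drop in power is the whole cost.

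**2. What differential loss could do.** The documents give no visit correlations and no loss pattern, so everything in this step is assumed:

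- 40 per arm, SD 17.5 at each visit, correlation between adjacent visits 0.8 or 0.9, decaying with lag.
- Treatment effect growing linearly: one third at day 30, two thirds at day 60, full at day 90.
- Scores complete to day 60. Probability of a missing day-90 score = 1 / (1 + exp(1.5 − s·z)), where z is the day-60 score minus the overall mean, divided by 17.5. s = −1 means low scorers leave, 0 means loss is unrelated to score, +1 means high scorers leave.
- 4,000 runs per scenario; 20% to 26% missing on average. Monte Carlo error about 4.3 / √4000 = 0.07 points.

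The interim-score estimate comes from a regression on arm, baseline, day 30 and day 60, which is equivalent to the likelihood estimate for this kind of monotone loss. Mean estimates, correlation 0.8 / 0.9:

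| Loss pattern | True difference | Observed day-90 scores only | Using interim scores |
|---|---|---|---|
| Low scorers leave both arms | 0 | 0.03 / 0.08 | 0.02 / 0.09 |
| | 12.4 | 11.67 / 11.45 | 12.42 / 12.33 |
| Low scorers leave placebo; unrelated on maraviroc | 0 | −2.68 / −3.04 | 0.03 / −0.05 |
| | 12.4 | 9.37 / 8.96 | 12.41 / 12.40 |
| Low scorers leave placebo; high scorers leave maraviroc | 0 | −5.26 / −6.08 | 0.09 / −0.06 |
| | 12.4 | 6.32 / 5.45 | 12.43 / 12.38 |

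Shortfall from 12.4 in the three patterns: 0.7 to 1.0, 3.0 to 3.4, and 6.1 to 7.0 points. Swapping the arm labels when there is no true effect reverses the sign, so the same mechanisms can also create an apparent benefit.

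**3. The mixed model as named.** With only time point and group as fixed effects, the group coefficient is one difference averaged over the visits in the model. Under the linear growth assumed above and complete data:

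- Days 30, 60 and 90: (4.13 + 8.27 + 12.4) / 3 = 8.3 points.
- With baseline also in the outcome: (0 + 4.13 + 8.27 + 12.4) / 4 = 6.2 points.

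Neither is the day-90 difference. The model needs a group-by-visit term to give it.

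**The case against.** The strongest reply is that the plan already names a mixed model. Its section covers primary and secondary outcomes, and FMA-UE is a natural candidate because the motor learning score is measured only at baseline and day 90. A likelihood mixed model imputes nothing, so it is compatible with the quoted rule. This stands, and it makes the repair easy. It does not remove the point: the t-test is what the text attaches to the primary outcome, and the model as listed does not target day 90.

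Several stronger readings are tempting and are not supported:

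- *16 of 80 day-90 scores will be missing.* The 20% covers exclusions as well as dropout, so the missing share may be smaller.
- *Only people who completed treatment are analysed.* Those who stop treatment are asked to stay and count if they have a day-90 score. Home visits, where an examiner can score FMA-UE, are offered as well as phone contact. Whether a phone contact could yield a score is not stated.
- *Any loss related to recovery invalidates the test.* When low scorers leave both arms alike and there is no true effect, the comparison stays centred on zero.
- *The at-least-one-dose rule breaks intention-to-treat.* It makes a modified set, openly defined. With double blinding and identical capsules this is a minor labelling matter.
- *Handling of deaths and tipping-point analysis are missing.* These may properly sit in the statistical analysis plan, which is not shown.

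The simulation is also kind to the repair: loss was generated from the day-60 score, so an analysis using that score recovers the truth by construction. Loss caused by events after day 60 carries no such guarantee.

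**Conclusion.** The point holds for the primary analysis as written. The plan fixes a method that discards everyone without a day-90 score and leaves the day-30 and day-60 scores unused, while a suitable class of model is already named a few lines away.

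The size of the bias is not established. It ranges from none, if loss is unrelated to outcome, through roughly 1 to 3 points of 12.4 in the milder simulated patterns, to 6 to 7 in an extreme one where loss runs in opposite directions in the two arms. These figures rest on assumed correlations, an assumed strength of dependence and about 20% to 26% missing. A reader might infer that bias as large as the target effect is to be expected; the documents do not support that. The change should be made, but the defect is not known to be fatal.

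**What to change.** Replace the primary test and the missing-data sentence with a likelihood-based mixed model:

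- Outcome: FMA-UE at days 30, 60 and 90, in all randomised participants as allocated.
- Covariates: baseline FMA-UE and the two stratification factors (infarct side, finger extension).
- Terms: group, visit and group-by-visit, allowing for correlation within participant.
- Primary estimate: the day-90 group contrast.

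Keep the t-test on observed day-90 scores as a sensitivity analysis.

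The cost is wording and modest programming; N stays at 80 and no visit is added. Recruitment runs to December 2027 and the final analysis plan is to be validated before unblinding, so there is time. The downside is reliance on data being missing at random given the scores seen, which a sensitivity analysis should test. A participant with no score after baseline still adds no outcome information, so the effort to obtain day-90 scores in person or at home remains important.

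### The headline day-90 FMA-UE comparison is unadjusted although randomisation is stratified, and no test, covariate list or analysis set is named as deciding; the stratification-adjusted model in the ITT set should decide.

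*Protocol article*

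**What the plan says.** Under 'Statistical methods for primary and secondary outcomes' the article gives the main comparison: "The primary outcome (FMA-UE) will be compared between groups using a t-test or non-parametric equivalent". It states no condition for moving from one test to the other. It then adds an adjusted linear regression on infarct side and finger extension, "as well as other variables like CCR5-Δ32 loss-of-function mutation carrier status", so the covariate list is open. On populations it says: "Two analysis sets will be used: an intention-to-treat population (all randomised participants who received ≥1 dose, analysed per allocation", with a per-protocol set beside it that leaves out major deviations such as adherence below 80%. Neither set is called primary.

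Under 'Sample size estimate' the trial is sized as a single comparison of two means: "based on a MCID for FMA-UE of 12.4 points in the early subacute phase of stroke recovery", "a pooled SD of 17.5" and "a 5% type I error and 80% power and accounting for a 20% dropout or exclusion rate".

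Under 'Blinding and randomisation' allocation uses permuted blocks of 2, 4 and 6 within four strata, infarct side by finger-extension subscore. The same section says that the final SAP is validated before study unblinding.

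**The concern.** Stratified blocks make the arms nearly equal on infarct side and finger extension. If finger extension predicts day-90 FMA-UE, part of the outcome variance can no longer contribute to the difference between arms. An unadjusted t-test still counts that part in its standard error. The result is a test that rejects too rarely and a confidence interval that is too wide. The regression on the stratification factors removes the problem, yet the article places it second.

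The candidates also do not answer one question. The t-test and the regression estimate the mean difference on which the trial is sized; a rank test does not. The per-protocol set is selected after randomisation. Three tests in two sets give six results for one hypothesis. If they disagree, the conclusion depends on which is put forward.

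**Working it through.** **1. The plan's own figure.** Inputs from 'Sample size estimate': difference 12.4, SD 17.5, 5% type I error, 80% power, 20% loss. Sidedness is not stated; two-sided is assumed.

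n per arm = 2 × (1.960 + 0.842)² × (17.5/12.4)² = 31.3, rounded up to 32. The total is 64, and 64/0.80 = 80, which matches "We estimated a sample size of 80 participants". Exact t-test power with 32 per arm is 79.7%. A one-sided 5% test would need 26 per arm (52/0.80 = 65), so the figure of 80 fits a two-sided test.

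**2. True error of the unadjusted t-test.** Let finger extension explain a share R² of day-90 variance; this is not in the documents and is taken as 0.1–0.5. With arms balanced within strata, the mean difference has variance (1 − R²) × 2σ²/n, while the t-test uses 2σ²/n. Its true error is 2Φ(−1.999/√(1 − R²)), where 1.999 is the critical value on 62 df.

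Dropout after randomisation disturbs the balance a little. It was therefore also simulated: 80 randomised in stratified blocks of 2, 4 and 6, 64 kept at random, normal outcome, 10% or 20% excluded from per-protocol at random, 3,000 null trials per setting.

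| R² | t-test, formula | t-test ITT, simulated | adjusted ITT, simulated |
|---|---|---|---|
| 0.1 | 3.5% | 3.5–4.0% | 4.4–5.2% |
| 0.3 | 1.7% | 2.6–2.7% | 5.2–5.3% |
| 0.5 | 0.5% | 1.3–1.6% | 4.9–5.2% |

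**3. Power at R² = 0.3.** SE = 17.5 × √(2/32) = 4.375. λ = 12.4/4.375 = 2.834 for the planned effect, and 8/4.375 = 1.829 for 8 points, an assumed smaller effect. √(1 − 0.3) = 0.837.

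- Unadjusted, Φ((λ − 1.999)/0.837): Φ(0.998) = 84% and Φ(−0.20) = 42%. Simulated: about 83% and 41%.
- Adjusted, Φ(λ/0.837 − 2.00): Φ(1.39) = 92% and Φ(0.19) = 57%. Simulated: about 91% and 56%.

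The gain is about 8 points of power at the planned effect and 15 at 8 points, with the same patients.

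**4. Disagreement among the six analyses.** With 20% excluded from per-protocol at random and a 12.4-point effect, at least one analysis is significant and at least one is not in about 26–35% of trials as R² goes from 0.1 to 0.5. A repeat run gave 25%, 30% and 35% at R² 0.1, 0.3 and 0.5, which agrees within simulation error (about ±2 points).

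**5. If any significant result could be claimed.** Under stratified randomisation at least one of the six has p<0.05 in about 7–10% of null trials, two-sided. For the t-test or the adjusted regression in ITT alone it is about 5–6%.

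**The case against.** The strongest reply is that this is SAP detail. The article condenses a fuller protocol, and the final SAP is to be validated before unblinding. The trigger for a rank test, the covariate list and the order of the two sets are commonly settled there. Having both an ITT and a per-protocol set is conventional in a superiority trial and does not make them co-primary. The order of the text also suggests that the unadjusted comparison leads and the regression supplements it. All of this stands: the open choices alone would be no more than unfinished wording. What remains is what the article does state, namely that the headline comparison is unadjusted in a trial that stratifies on a likely prognostic factor.

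A reader might go further and infer that the plan carries a false-positive rate of 9–13%. The documents do not support that. They contain no rule that any significant result counts as success. Figures of that size arise for the six analyses when the stratified blocks are left out of the simulation; with them the figure is about 7–10%. It could reach about 10–15% only if optional prognostic covariates were also chosen freely in both sets. Treating the six as independent (1 − 0.95⁶ = 26%) is wrong because they are highly correlated. The rates are two-sided; false claims in favour of maraviroc from the six would be about 3–5% against a nominal 2.5%. A choice fixed blind keeps the error near 5%.

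It can also be said that a conservative t-test does no harm to type I error, and that at 12.4 points it still has about 83% power. Both are true. The cost is lost power, which matters most if the true effect is smaller than planned.

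**Conclusion.** The point holds as a matter of efficiency and of naming the deciding result, not as a demonstrated inflation of type I error. If finger extension is prognostic, the unadjusted ITT t-test runs at about 1–4% true error instead of 5%. At R² 0.3 it gives up about 8 points of power at 12.4 points and about 15 at 8 points against the stratification-adjusted model. With no result named as deciding, the six analyses would disagree on significance in about 26–35% of trials at the planned effect.

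These figures rest on 64 evaluable patients, R² of 0.1–0.5 for finger extension, normal outcomes, loss at random and, for the disagreement figure, 20% per-protocol exclusion at random. The documents give neither R² nor the exclusion share. If finger extension explained nothing, the t-test would run at about 5% and the adjusted model would have no real advantage.

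**What to change.** Before unblinding, state in the protocol and the SAP that the trial is decided by the between-arm mean difference in day-90 FMA-UE in the ITT set, from the linear model adjusted for infarct side and finger extension plus a closed list of baseline covariates, tested at two-sided 5% and reported with a 95% CI. Replace the open-ended covariate wording with that list. Describe the t-test, the rank test and the per-protocol analysis as supportive, unable to replace the deciding result.

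This takes a few sentences and needs no further patients or data. The small downside is that the sponsor can no longer fall back on another test or set.
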